Urinalysis findings showed more frequently positive blood urine tests in the Ad35.CS.01 groups than in the placebo group; this finding, which will be closely monitored in future studies, may be related to the unbalanced distribution of female subjects in the vaccine groups (47 to 60%) compared to placebo group (33%). All subjects with hematuria were in fact females with menses at the time of urine collection.

Immunogenicity was evaluated through assessment of both humoral immune response (anti-CS antibody levels) and cellular immune responses. Humoral responses against the vector were assessed as well by Ad35 neutralization assay.

Anti-CS antibodies were assessed at baseline, 1 month after each dose of vaccine (month 1, 2 and 7) and at month 6 (5 months after the second dose and prior to the last dose of vaccine) with an ELISA assay using a (NANP)6 peptide as capture antigen. The two lowest doses induced poor or no humoral responses. Anti-CS antibody levels following the  $10^8$  vp dose were not distinguishable from those recorded in the placebo group, while in the  $10^9$  vp dose approximately 30% of the subjects showed a  $\geq 4$  fold increase vs. baseline in anti-CS antibodies at any time during the study. On the contrary, in the remaining 2 groups, anti-CS antibodies levels showed a dose dependent increase, with 53% and 79% of subjects showing a  $\geq 4$  fold increase vs. baseline in the  $10^{10}$  and  $10^{11}$  vp dose group, respectively, 1 month after the second dose of vaccine. The immune response was further boosted by the third dose, particularly in the  $10^{11}$  vp dose group.

Cellular immune responses, evaluated through an IFN- $\gamma$  ELISPOT, are more difficult to interpret due to the small sample sizes, and sub-optimal collection and processing of PBMC's. However, the dose of  $10^{11}$  vp consistently provided some degree of cellular response at all time points evaluated.

Anti-Ad35 antibodies were elicited in a minority of subjects. The responses showed some level of dose-dependency, with no sign of interference with the anti-CS immunogenicity.

In conclusion, the administration of Ad35.CS.01 induces an antibody response against the CS protein in a dose dependent way. Priming is successfully achieved in most of the subjects receiving the doses of  $10^{10}$  and  $10^{11}$  vp, with higher titers observed in the  $10^{11}$  vp dose group. Boosting with further dose(s) of Ad35.CS.01 has proven to be possible in this study, particularly at the higher dose. Additional studies are warranted to assess whether other boosting modalities can be used to achieve higher humoral responses.

## **1.2. Rationale for the study and study design**

### **1.2.1. Rationale for the study**

GSK Biologicals in collaboration with MVI and Crucell is developing an Ad35.CS.01 prime-RTS,S/AS01B boost immunization regimen for prevention of malaria due to *P. falciparum* in infants and children living in malaria endemic areas.

While both RTS,S/AS01B and Ad35.CS.01 candidate malaria vaccines tested in this study have been administered to humans before, this trial will be the first one where they are combined in one immunization schedule.

### **1.2.2. Rationale for the study design**

This study is designed to evaluate safety, reactogenicity, immunogenicity and efficacy of Crucell's candidate replication deficient adenovirus type 35 circumsporozoite malaria vaccine (Ad35.CS.01) administered intramuscularly followed one month later by two doses of GSK Biological's malaria candidate vaccine RTS,S/AS01B administered intramuscularly at one month intervals, compared to three doses of RTS,S/AS01B administered intramuscularly at one month intervals in healthy malaria-naïve volunteers aged 18 to 50 years. The sporozoite challenge model, in the RTS,S/AS candidate vaccine development program, has demonstrated a high relevance in its ability to predict efficacy under conditions of natural exposure in malaria-endemic countries. Approximately 168 participants will be enrolled in the study. Three cohorts of approximately equal size will be enrolled, vaccinated then challenged separately. This design takes into account logistical restrictions on the size of human challenge procedures and allows for a futility analysis to be conducted after the results of the malaria challenge in the first cohort. The proposed study design is such that the sample size will provide 80% power to demonstrate a 50% increase in efficacy of an immunization regimen including an initial dose of Ad35.CS.01 over efficacy of a regimen based on RTS,S/AS01B alone, assuming 50% vaccine efficacy of the RTS,S/AS01B group over challenge infectivity controls.

The study design is similar to that of other past studies successfully conducted. Healthy adults will be enrolled and followed up in closely controlled conditions by investigators

experienced in *P. falciparum* challenge studies. Immunological investigations are planned with the intent to characterize qualitatively and quantitatively the immune response induced by the immunization regimen and assess the presence of a correlation of specific effector immune function(s) with protection against malaria infection in the sporozoite challenge model. Protection will be evaluated by the proportion of immunized participants who remain free of *P. falciparum* infection following sporozoite challenge and by a delay in the pre-patent period leading to infection.

## **2. OBJECTIVES**

### **2.1. Primary objective**

- To compare the efficacy (occurrence of *P. falciparum* parasitemia, assessed by blood slide) of an immunization regimen comprising of one dose of Ad35.CS.01 followed one month later by two doses of RTS,S/AS01B administered at one month intervals, with that of three doses of RTS,S/AS01B administered at one month intervals, in healthy malaria-naïve volunteers aged 18-50 years in the sporozoite challenge model.
- To assess the safety (reactogenicity, unsolicited adverse events, SAEs up to 30 days post last vaccination [day of vaccination and 29 subsequent days], SAEs up to study conclusion) of an immunization regimen comprising of one dose of Ad35.CS.01 followed one month later by two doses of RTS,S/AS01B administered at one month intervals in healthy malaria-naïve volunteers aged 18-50 years.

Refer to Section 10.1 for the definition of the primary endpoints.

### **2.2. Secondary objectives**

- To compare the efficacy (time to *P. falciparum* parasitemia, assessed by blood slide) of an immunization regimen comprising of one dose of Ad35.CS.01 followed one month later by two doses of RTS,S/AS01B administered at one month intervals, with that of three doses of RTS,S/AS01B administered at one month intervals, in healthy malaria-naïve volunteers aged 18-50 years in the sporozoite challenge model.
- To assess the humoral and cell-mediated immune response to malaria and hepatitis B antigens (by ELISA, ICS and ELISPOT) induced by one dose of Ad35.CS.01 followed one month later by two doses of RTS,S/AS01B administered at one month intervals in healthy malaria-naïve volunteers aged 18-50 years.
- To assess the humoral immune response to adenovirus antigen induced by one dose of Ad35.CS.01 followed one month later by two doses of RTS,S/AS01B administered at one month intervals in healthy malaria-naïve volunteers aged 18-50 years.

Refer to Section 10.2 for the definition of the secondary endpoints.

### **2.3. Exploratory objectives**

- To compare the efficacy (occurrence of *P. falciparum* parasitemia and time to *P. falciparum* parasitemia, assessed by PCR) of an immunization regimen comprising of one dose of Ad35.CS.01 followed one month later by two doses of RTS,S/AS01B

- To assess the immune response to malaria, hepatitis B and adenovirus antigens (by various methods including high-throughput technologies such as microarray analysis and deep sequencing, as part of a systems biology approach) induced by one dose of Ad35.CS.01 followed one month later by two doses of RTS,S/AS01B administered at one month intervals in healthy malaria-naïve volunteers aged 18-50 years.

### 3. STUDY DESIGN OVERVIEW

[figure not shown]

- 09-JUN-2011  
ac77581444799105ae4098b6a1e70d5be1264a8b

- Challenge epoch: Challenge starting Visit 20 (Day 77) and ending Visit 40 (Day 105).
- Follow-up epoch: Follow-up starting Visit 41 (Day 140) and ending Visit 42 (Day 236).

**Table 3 Study groups and epochs foreseen in the study**

| Study groups         | Number of subjects      | Age (Min/Max) | Epochs          |                   |                 |                 |
|----------------------|-------------------------|---------------|-----------------|-------------------|-----------------|-----------------|
|                      |                         |               | Screening epoch | Vaccination epoch | Challenge epoch | Follow-up epoch |
| RRR                  | 84                      | 18 - 50 years | x               | x                 | x               | x               |
| ARR                  | 84                      | 18 - 50 years | x               | x                 | x               | x               |
| Infectivity controls | 4 - 6 per challenge day | 18 - 50 years | x               |                   | x               | x               |

ARR = first dose with Ad35.CS.01, second and third doses with RTS,S/AS01B

RRR = three doses of RTS,S/AS01B

- Control: active control. The group receiving three doses of RTS,S/AS01B will be the comparator group. In addition, there will be infectivity controls for the challenge epoch (i.e. volunteers who will not receive any immunization but will be subjected to the sporozoite challenge).
- Vaccination schedule: 0-1-2 months followed by a challenge 21 days (3 weeks)  $\pm$  7 days after the third vaccination.
- Safety considerations:

Vaccination and challenge will be performed in a staggered fashion. Three cohorts (Cohort A, B and C) of approximately equal size will be enrolled, vaccinated and challenged separately. Each cohort which enters the vaccination phase will include approximately 56 subjects. Among the 56 vaccinated individuals a random selection of subjects eligible for challenge will be done according to the local SOP to ensure that a maximum of 46 vaccinated individuals (balanced by group) will progress to the challenge phase. The remaining subjects will not be challenged but they will be followed for safety and immunogenicity up to 6 months after the last vaccination (Study Day 236). Vaccination and challenge will be performed first in Cohort A. Safety and efficacy data post-challenge from this initial cohort and 4 to 6 infectivity controls will be reviewed prior to the start of vaccination in Cohorts B and C, based on pre-defined group holding criteria for safety review (see Section 5.4.4.1) and pre-defined criteria for efficacy futility analysis (see Section 5.4.4.2). Vaccination and challenge of subjects in Cohorts B and C is likely to take place in parallel at two different sites (see Section 4.2 for more details).

In addition, the Principal Investigator (PI) will have the responsibility to withdraw from further vaccination individual study participants who present at least one of the pre-defined stopping rules for individual subjects (see Section 5.4.4.1).

- Safety and immunogenicity will be evaluated during the study through 6 months after the last vaccination (Study Day 236).
- Study groups: refer to Table 4.

**Table 4 Study groups**

| Treatment name          | Vaccine/Product name | Study groups |     |                      |
|-------------------------|----------------------|--------------|-----|----------------------|
|                         |                      | RRR          | ARR | Infectivity controls |
| Ad35.CS.01              | Ad35.CS.01           |              | x   |                      |
| RTS,S/AS01 B | RTS,S                | x            | x   |                      |
|                         | AS01 B    | x            | x   |                      |

- Treatment allocation: randomised (1:1).
- Blinding: observer-blind as to immunization regimens (see [Table 5](#)).

**Table 5 Blinding of study epochs**

| Study Epochs      | Study groups         | Blinding       |
|-------------------|----------------------|----------------|
| Screening epoch   | Immunization groups  | N/A            |
|                   | Infectivity controls | N/A            |
| Vaccination epoch | Immunization groups  | observer-blind |
|                   | Infectivity controls | N/A            |
| Challenge epoch   | Immunization groups  | observer-blind |
|                   | Infectivity controls | open           |
| Follow-up epoch   | Immunization groups  | open           |
|                   | Infectivity controls | open           |

N/A: Not applicable

- Blood sampling: refer to [Table 6](#).

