### **5.3. Method of blinding**

The study will be conducted in an observer-blind manner.

Data will be collected in an observer-blind manner. By observer-blind, it is meant that during the course of the study, the vaccine recipient and those responsible for the evaluation of any study endpoint (e.g. safety, reactogenicity, and efficacy) will all be unaware of which vaccine was administered. To do so, vaccine preparation and administration will be done by authorised medical personnel who will not participate in any of the study clinical evaluation assays.

The laboratory in charge of the laboratory testing will be blinded to the treatment, and codes will be used to link the subject and study (without any link to the treatment attributed to the subject) to each sample.

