**5.4.4.1.3. Cohort A data review by the SMC prior to vaccinations in Cohort B and Cohort C:**

An interim unblinded SMC report including all available safety and reactogenicity data, will be produced by an independent statistician according to an agreed pre-defined Report and Analysis Plan, after the Cohort A has completed the one month post challenge visit. The SMC will review this report prior to authorizing vaccinations to proceed in Cohort B and Cohort C. Vaccination of the next cohort of study participants can be put on hold by the SMC if either of the following sets of holding criteria described below is met:

*Holding rules*

- Solicited local adverse events:
  - More than 25% of Ad35.CS.01 doses are followed by Grade 3 solicited local adverse event beginning within 2 days after Ad35.CS.01 vaccination (day of vaccination and one subsequent day) and persisting at Grade 3 for > 2 consecutive days
  - More than 25% of first doses of RTS,S/AS01B in subjects having received Ad35.CS.01 are followed by Grade 3 solicited local adverse event beginning within 2 days after vaccination (day of vaccination and one subsequent day) and persisting at Grade 3 for > 2 consecutive days
  - More than 25% of second doses of RTS,S/AS01B in subjects having received Ad35.CS.01 are followed by Grade 3 solicited local adverse event beginning within 2 days after vaccination (day of vaccination and one subsequent day) and persisting at Grade 3 for > 2 consecutive days
- Solicited systemic adverse events:
  - More than 25% of Ad35.CS doses are followed by Grade 3 solicited systemic adverse event estimated to be related to vaccination beginning within 2 days

after Ad35.CS.01 vaccination (day of vaccination and one subsequent day) and persisting at Grade 3 for > 2 consecutive days

- More than 25% of first doses of RTS,S/AS01B in subjects having received Ad35.CS.01 are followed by Grade 3 solicited systemic adverse event estimated to be related to vaccination beginning within 2 days after vaccination (day of vaccination and one subsequent day) and persisting at Grade 3 for > 2 consecutive days
- More than 25% of second doses of RTS,S/AS01B in subjects having received Ad35.CS.01 are followed by Grade 3 solicited systemic adverse event estimated to be related to vaccination beginning within 2 days after vaccination (day of vaccination and one subsequent day) and persisting at Grade 3 for > 2 consecutive days

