#### **5.4.4.2. Efficacy futility review**

The planned futility analyses will be conducted by an external statistician who will ensure the maintenance of the blinding of all parties involved in the trial.

Futility analyses will be conducted on efficacy data collected up to 28 days post-challenge (Study Day 105) for the first 46 subjects vaccinated and challenged (Cohort A).

Vaccination of Cohorts B and C will only proceed if the calculated point estimate of increase of vaccine efficacy (VE) in the Ad35.CS.01 – RTS,S/AS01B group over RTS,S/AS01B alone is over 0%, providing a 4 % risk of stopping the trial if the true increase in VE is 50%, assuming an attack rate of 50% in the RTS,S/AS01B group. The probability to stop for futility using these criteria if true increase in vaccine efficacy is 0% is of 40%. The increase in VE of the Ad35.CS.01 group over the RTS,S/AS01B alone

group is defined as  $100 * (1 - \text{AR}_{\text{Ad35.CS.01}} / \text{AR}_{\text{RTS,S}})$  where AR is the attack rate in the 2 groups.

If the above criteria are not met, then vaccination of consecutive cohorts will be performed only if there is agreement between all parties and the study PI.

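### Table 5 makes Cohort A open from Day 140, before any Cohort B or C subject is challenged, against the protocol's other blinding rules

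*Protocol*

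**What the plan says.** Table 5 in Section 3, repeated as Synopsis Table 3, assigns blinding by epoch. For the vaccine groups it gives "Challenge epoch | Immunization groups | observer-blind" and then "Follow-up epoch | Immunization groups | open". Section 3 runs the challenge epoch from Day 77 to Day 105 and the follow-up epoch from Day 140 to Day 236. These are days on each subject's own clock. Neither table makes the change to open depend on the cohort.

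The cohorts are sequential. Under Table 3 in Section 3, Cohort A's post-challenge data "will be reviewed prior to the start of vaccination in Cohorts B and C". Section 5.4.4.1.3 places the safety report for that review "after the Cohort A has completed the one month post challenge visit". Section 5.4.3 has WRAIR challenge Cohort A and then Cohort B, with Cohort C at the University of Maryland.

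Four other places point the other way:

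- Section 5.3 says that, "during the course of the study, the vaccine recipient and those responsible for the evaluation of any study endpoint", are kept unaware of the vaccine given.
- Section 5.4.4.2 assigns the futility analysis to "an external statistician who will ensure the maintenance of the blinding of all parties involved in the trial".
- Section 10.7.2 releases summary interim results only, with no individual unblinded.
- The glossary entry on blinding keeps the blinding level for the whole trial. It allows unblinding once data are clean, or when a serious adverse event requires it.

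**The concern.** Site staff know each Cohort A outcome, because they take the smears and treat the infections. The allocation list is the only thing that separates this from an interim efficacy result by arm. If it becomes available from Day 140, the result can be computed locally while two thirds of the primary data are still to come, and part of what the external statistician is meant to protect is lost.

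Several steps that feed the primary endpoint or its analysis set rest on judgement:

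- The principal investigator decides who is symptomatic, which doubles the blood volume read (5.4.3.4), and symptoms trigger more frequent films (5.4.3.5).
- Challenge of a volunteer with a minor illness is at the investigator's discretion (5.4.3.1).
- Some individual stopping rules turn on whether an event is judged related to vaccination (5.4.4.1.3).
- The detailed list of reasons for ATP elimination is fixed only at data cleaning (6.7.1), and efficacy is analysed on the ATP cohort (10.8.2).

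**Working it through.** **Plan's own figure.** The protocol gives no figure for the overlap. Its power figure is not at issue and reproduces: exact enumeration of the two-sided Fisher test with 69 per arm and attack rates of 50% and 25% gives 82.3%, against 82% in Section 10.4.

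**Inputs**
- Start of the open epoch: Day 140. Challenge: Day 77. End of the endpoint window: Day 105 (Section 3).
- Earliest review: after Cohort A's Day 105 visit (5.4.4.1.3).
- Visit windows (Table 11): dose 1 to 2 and dose 2 to 3, 28 ± 4 days each; dose 3 to challenge, 21 ± 7; Visit 40 to Visit 41, 35 ± 7.
- Gap g from Cohort A's Day 105 to the first dose in B/C: not in the documents. Assumption: g ≥ 0, shown for 0 to 90 days.

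**Mapping the two clocks.** Cohort A day = 105 + g + B/C day. Hence:
- B/C day when Cohort A opens = 140 − 105 − g = 35 − g
- B/C challenge = Cohort A Day 105 + g + 77 = 182 + g
- End of the B/C endpoint window = Cohort A Day 105 + g + 105 = 210 + g

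| g (days) | B/C position when A opens | B/C challenge (A day) | B/C Day 105 (A day) | Lead over challenge | Lead over end of window |
|---|---|---|---|---|---|
| 0 | Day 35 | 182 | 210 | 42 | 70 |
| 30 | Day 5 | 212 | 240 | 72 | 100 |
| 60 | 25 days before dose 1 | 242 | 270 | 102 | 130 |
| 90 | 55 days before dose 1 | 272 | 300 | 132 | 160 |

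The leads are 42 + g and 70 + g days, so both are smallest at g = 0. If g exceeds 35, Cohort A opens before B and C are vaccinated at all.

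**Adverse visit windows.** The fastest path from dose 1 to challenge in B/C is 24 + 24 + 14 = 62 days. The slowest Visit 40 to Visit 41 in Cohort A is 35 + 7 = 42 days. Even at g = 0, Cohort A is open 62 − 42 = 20 days before the first B/C challenge.

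**Size.** With 46 challenged per cohort, 46 × 3 = 138. Cohort B, read at Cohort A's site, is 46 of 138. B and C together are 92 of 138 = 67%. Cohort A's by-arm result would rest on 46 / 2 = 23 per arm.

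**The case against.** The strongest reply is that a single table word carries the point. No passage sends Cohort A codes to site staff or volunteers at Day 140. The only routes described for releasing an individual code are Sections 8.7 and 8.8. The glossary ties unblinding to clean data, and laboratory blinding (5.3, Appendix C) has no end date. So a reader might infer that slide readers will be told the codes, but the documents do not say so. What stands is narrower: Table 5 permits disclosure, does not define open or name recipients, and conflicts with the other passages. They do not override it.

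A reader might also infer that B and C are unmasked. They are not: knowing Cohort A's codes does not show who received what in the later cohorts. Without those codes, staff cannot deliberately treat the arms differently. Positivity also needs at least two unambiguous parasites, films are archived, and the cut to 46 per cohort is by random selection balanced by group. This limits the risk to expectation and operational effects.

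Some group-level information is released by design. Section 10.7.2 allows summary results to be communicated, and proceeding under the rule in 5.4.4.2 signals a point estimate above zero. What Table 5 adds is the possibility of the by-arm counts being known at the site.

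The open period might be taken to weaken a primary safety endpoint through late causality or pIMD assessment. Section 10.1 does not support that. Its SAE endpoint for the whole study is occurrence; causality is not part of it and pIMDs are not named.

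**Conclusion.** The point holds in a limited form. As written, Table 5 and Synopsis Table 3 open Cohort A at least 42 nominal days before any B or C challenge and 70 before their endpoint window ends, whatever the review gap. They cannot be followed together with the glossary and Sections 5.3, 5.4.4.2 and 10.7.2. Exposure is most direct for Cohort B (46 of 138). It reaches 92 of 138 only if the knowledge passes to the second site.

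The timing rests on B/C dose 1 not preceding Cohort A's Day 105 visit, which the protocol requires, and on open having its ordinary meaning, which the protocol does not spell out. Whether Cohort A opens part-way through B and C vaccination or before it begins depends on a gap that the documents do not give. The size of any bias cannot be computed from the documents, and none is claimed.

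**What to change.** In Table 5 and Synopsis Table 3, set the follow-up epoch to observer-blind for the vaccine groups until all cohorts have completed Day 105 and the database for the all-cohort primary analysis is locked. State who may receive codes once it is open. Leave SAE and emergency unblinding (8.7, 8.8) unchanged.

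The earliest opening for Cohort A then moves from Day 140 to Day 210 + g, plus the time to lock. Its Day 140 visit is always blinded. Its Day 236 visit is also blinded once g exceeds 236 − 210 = 26 days, or sooner if lock takes time. Sample size, alpha and the 82% power do not change. The cost is an amendment to two tables and later disclosure of allocation to Cohort A, if disclosure was intended. The change should be made before Cohort A reaches Day 140, because disclosure cannot be reversed.
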